### Criteria for discontinuing or modifying allocated interventions {11b}

Interventions will be discontinued when a participant no longer wants to continue the intervention or when a participant is an early therapy completer. The interventions that are tested are found to be feasible and safe in this population and the study is situated in routine clinical practice.

### Strategies to improve adherence to interventions {11c}

Both formulation-based CBTp and Feeling Safe-NL involve shared decision-making and tailoring of CBT-techniques to each individual patient to promote adherence and outcomes. Therapists and peer counsellors generally see participants at their local community mental health team, but home visits are possible to improve adherence to the interventions.

### Relevant concomitant care permitted or prohibited during the trial {11d}

Standard care will continue as usual and will be monitored by the research team.

### Provisions for post-trial care {30}

There are no provisions for post-trial care since the interventions are found to be feasible and safe in this population and the study is situated in routine clinical practice. Usual care will continue when the trial ends.

### Outcomes {12}

The primary outcome will be psychological wellbeing (Warwick-Edinburgh Mental Well-Being Scale, WEMWBS)^28^ over time (assessed using the overall effect over time from baseline to 18-month follow-up and the effects at each timepoint) [27].

The secondary outcomes include persecutory delusion severity (Psychotic Symptom Rating Scale-Delusion Subscale, PSYRATS-DS) [42], general paranoid ideation (Revised-Green et al. Paranoid Thoughts Scale, R-GPTS), patient chosen outcomes (CHoice in Outcome In Cognitive behaviour therapy for psychosEs, CHOICE) and activity (time budget). Outcomes for conviction of the main persecutory delusion will also be dichotomized in line with the Feeling Safe Study (in which recovery is defined as conviction falling below 50%) [5].

We will also assess several mediators: trauma imagery (Trauma Screening Questionnaire, TSQ; PTSD Checklist for DSM-5, PCL-5) [43–45], insomnia (Insomnia Severity Index, ISI) [46], self-esteem (Brief Core Schema Scales, BCSS) [47], worry (Dunn Worry Questionnaire) [48], anomalous experiences (Voices Impact Scale, VIS; a publication concerning the psychometrics is underway), safety-seeking behaviours or defences (Oxford Agoraphobic Avoidance Scale, O-AS [49]; Oxford Paranoia Defence Behaviours Questionnaire, OPDBQ; Lambe et al., *in prep*), reasoning biases (Fast and Slow Thinking Questionnaire, FaST; Explanations of Experiences, EofE, Maudsley Assessment of Delusions Schedule-Possibility of being Mistaken, MADS-PM) [50–52], personal recovery (Questionnaire about the Process of Recovery, QPR) [53], and resilience (The Brief Resilience Scale, BRS) [54].

Other study parameters include the therapeutic relationship (Counsellor Rating Form-Short, CRF-S) [55] and working alliance (Working Alliance Inventory-Short Form Revised, WAI-SR) [56]. For the health-economic evaluation we will use the Treatment Inventory of Costs in Patients with psychiatric disorders (TIC-P) and the standardized EuroQol  5-Dimension 5-Level questionnaire (EQ-5D-5L) at baseline and after 6 (post-intervention) 12 and 18 months.

### Participant timeline {13}

Following enrolment, participants will be allocated to formulation-based CBTp or the Feeling Safe-NL Programme. Assessments will be carried out at baseline and after 6 (post-intervention) 12 and 18 months. A schematic diagram is provided in Table 1.

**Table 1 Tab1:**
[figure not shown]
Overview of the procedures and instruments used at the different time points

### Sample size {14}

The sample size for longitudinal intention-to-treat (ITT) analyses with linear mixed models (LMM) was calculated according to the method presented by Liu and Liang (1997) and based on data from previous RCTs [5, 13–15, 24]. Although an ITT analysis with LMM is robust against moderate attrition, we aim to include an additional 10% to compensate for potential dropout. With alpha = 0.05; beta = 0.2; rho = 0.5; 3 repeated follow-up assessments and 10% drop-out; we will need 95 participants in each arm to detect small to medium effects (0.35). Therefore, we aim to include 190 participants.

### Recruitment {15}

Our strategy for achieving adequate participant enrolment to reach the target sample size is to recruit at several large mental healthcare institutions that collaboratively offer care to more than 200,000 patients. Additionally, we work with a committed group of peer counsellors and therapists and trained trial assessors who are involved in informing patients and community health team staff.

## Assignment of interventions: allocation

### Sequence generation {16a}

Patients will be randomized by our independent randomization bureau using a scientific randomization program on the internet (http://www.randomizer.org). The allocation sequence ensures an equal assignment to both interventions for each site.

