### Trial design {8}

A pragmatic single-blind superiority randomized controlled trial with two parallel groups. Patients will be randomized (1:1) to the Feeling Safe-NL Programme or formulation-based CBTp. Measurements are conducted at baseline, 6-, 12-, and 18-month follow-up (see Fig. 1). In both arms, people will receive weekly therapy sessions over a period of 6 months. To support the therapies in both arms, optional self-monitoring is available via brief questionnaires of which the outcomes are visualized. This supports the participant and therapist in monitoring change and shared decision-making.

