## Methods: participants, interventions and outcomes

### Study setting {9}

Participants will be recruited from outpatient services of several large mental health organizations in the Netherlands (Parnassia Groep, Altrecht and GGZ Oost Brabant) that offer care to people with persecutory delusions.

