## Statistical methods

### Statistical methods for primary and secondary outcomes {20a}

The primary continuous outcomes for mental wellbeing will be analyzed with linear mixed models (LMM) with outcome measurement (at the three follow-up timepoints) as the dependent variable and based on the intention-to-treat (ITT) principle. Baseline values will be added as covariates, time as a categorical variable, and treatment condition as a fixed effect. The regression coefficient of the LMM will be used as the between-group effect size (Feeling Safe-NL vs formulation-based CBTp) since this is the estimated difference in results between the groups.

The secondary continuous outcomes for the persecutory delusion, general paranoid ideation, patient-chosen therapy outcomes and activity will also be analyzed with LMM with outcome measurements (at the three follow-up timepoints) as the dependent variable and based on the intention-to-treat (ITT) principle. Baseline values will be added as covariates, time as a categorical variable, and treatment condition as a fixed effect. Between-group effect sizes (Feeling Safe-NL vs formulation-based CBTp) will be derived from the regression coefficient of the LMM. Outcomes for conviction of the main persecutory delusion (PSYRATS-DS) will also be dichotomized with recovery being defined as conviction falling below 50%. Logistic generalized estimating equations (GEE) with exchangeable correlation structure ITT analysis will be used to examine the effects on dichotomous outcomes, since GEE is reported to be a better estimator of effects in dichotomous outcomes than LMM [66]. Effects for Feeling Safe-NL vs formulation-based CBTp will be computed for “condition” (overall effect) and with interaction effects between time and condition for post-therapy (6-month follow-up; change during the treatment period) and for 12- and 18-month follow-up (change during the follow-up periods).

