### Methods for additional analyses (e.g. subgroup analyses) {20b}

N/a. There is no plan for any additional analyses.

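### Allocation is balanced within site, but the listed model terms leave site out, so the treatment effect's standard error will be somewhat too large if sites differ in outcome

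*Protocol article*

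**What the plan says.** Trial design {8} sets the ratio: "Patients will be randomized (1:1) to the Feeling Safe-NL Programme or formulation-based CBTp". Sequence generation {16a} adds the restriction: "The allocation sequence ensures an equal assignment to both interventions for each site". How this is achieved (blocks, separate lists) is not described. Study setting {9} states: "Participants will be recruited from outpatient services of several large mental health organizations in the Netherlands", and names three organisations. It does not say whether a site is an organisation or a local service.

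For the analysis, section {20a} gives the LMM terms once for the primary outcome and again, in the same words, for the secondary continuous outcomes: "Baseline values will be added as covariates, time as a categorical variable, and treatment condition as a fixed effect". It later adds time-by-condition interactions for the effects at each follow-up. For recovery defined by delusional conviction it says: "Logistic generalized estimating equations (GEE) with exchangeable correlation structure ITT analysis will be used to examine the effects on dichotomous outcomes". Site appears in none of these. The random-effects or covariance structure of the LMM is not described. Section {20b} says: "There is no plan for any additional analyses", so no site-adjusted sensitivity analysis is stated either.

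**The concern.** When allocation is forced to be equal within a factor, differences between the levels of that factor cannot contribute to the difference between arms. The true sampling variance of the treatment effect is then smaller than under simple randomisation. A model that omits the factor does not know this: it leaves the between-site variance in the residual and reports a standard error that is too large.

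At stake are confidence intervals slightly wider than the design warrants, a test that rejects a true null less often than 5%, and some lost power. The comparator is an active guideline therapy whose content, by the protocol's own account, partly overlaps with the intervention, and the trial is sized for 80% power at 0.35 SD, so there is little power to give away.

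**Working it through.** **Inputs from the documents.** Sample size {14}: "alpha = 0.05; beta = 0.2; rho = 0.5", then "3 repeated follow-up assessments and 10% drop-out", an effect of 0.35 and 95 per arm. Sidedness of alpha is not stated.

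**The plan's own figure.** With exchangeable correlation, the variance of a patient's mean over three follow-ups, in units of the single-measurement variance, is (1 + 2 × 0.5)/3 = 2/3. Then

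n per arm = 2 × (1.960 + 0.842)² × (2/3) / 0.35² = 85.43, and 85.43/0.9 = 94.9, so 95.

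The stated number reproduces with two-sided alpha. One-sided alpha gives 67.3, or 74.8 after dropout, and does not. Site plays no part in this calculation.

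**Effect of leaving site out.** Let s be the share of the variance of the patient mean that lies between sites. The documents give no value, so 0 to 10% is assumed. With exact balance within site:

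- Standard error reported without site, at 86 evaluable per arm: SE_m = √(2/3) × √(2/86) = 0.1245.
- True standard error: SE_t = SE_m × √(1 − s).
- Overstatement: 1/√(1 − s) − 1.
- True type I error without site: 2 × [1 − Φ(1.96/√(1 − s))].
- Power without site: Φ[(0.35 − 1.96 × SE_m)/SE_t].
- Power with site: Φ[0.35/SE_t − 1.96].

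At s = 10%: SE_t = 0.1245 × 0.9487 = 0.1181. Power without site is Φ[(0.35 − 0.2440)/0.1181] = 81.5%. Power with site is Φ[2.963 − 1.96] = 84.2%.

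| Assumed s | SE too large by | True type I error | Power without site | Power with site | Points lost |
|---|---|---|---|---|---|
| 0% | 0% | 0.050 | 80.3% | 80.3% | 0 |
| 1% | 0.5% | 0.049 | 80.4% | 80.7% | 0.3 |
| 2% | 1.0% | 0.048 | 80.5% | 81.0% | 0.5 |
| 5% | 2.6% | 0.044 | 80.9% | 82.2% | 1.4 |
| 10% | 5.4% | 0.039 | 81.5% | 84.2% | 2.7 |

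Points lost are taken before rounding.

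**Simulation check.** 172 evaluable patients were placed in three sites of 86, 52 and 34 (assumed sizes), with allocation permuted to exact balance within site. The patient mean was analysed with and without site, in 10,000 runs for alpha and 5,000 for power. At s = 5%, type I error was 0.043 without site and 0.049 with it. At s = 10% it was 0.040 and 0.050, and power was 81.8% and 84.6%. At s = 0 both models gave 0.045, about two Monte Carlo standard errors below 0.05 (one is √(0.05 × 0.95/10,000) = 0.0022), with no difference between them. The simulation agrees with the formula on direction and size.

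These figures are for the linear model on the patient mean. Like the sample size calculation, they ignore the gain from the baseline covariate. No size was computed for the GEE.

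**The case against.** The strongest objection is that this is an omission and not a contradiction. Section {20a} does not exclude site, a journal article condenses the full plan, and stratification covariates are often settled in an analysis plan that is not shown here. The term list is also visibly incomplete: interactions are added later and no random-effects structure is given. A reader might infer that the model is a closed list that rules site out; the text does not support that. What remains is that the article does not defer its covariates. It names them twice, specifies the GEE down to its correlation structure, and omits the one factor that it says restricts the allocation. An analyst following the text as written would fit models that do not reflect the design.

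The objection on size is also fair. The site share is an assumption. What counts is the share left after adjustment for baseline wellbeing, in a sample selected for low wellbeing and with every therapist delivering both treatments. It could be near zero, and the effect then vanishes.

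Three further inferences should be resisted:

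- **That stated confidence intervals or error bars are wrong.** The documents state none. The point concerns the standard errors that the planned models would produce.
- **That site adjustment lifts power from 80% to as much as 84%.** Balance within site also helps the unadjusted estimator, so the fair comparison at a 10% share is 81.5% against 84.2%.
- **That adding site to the GEE changes only precision.** Odds ratios are non-collapsible, so the quantity estimated changes too.

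**Conclusion.** The point holds, and it is small. The allocation uses site and the listed model terms do not. If sites differ in outcome, the planned standard errors err on the large side. For an assumed site share of 0 to 10%, they are overstated by 0 to 5.4%, the two-sided test runs at 5.0% down to 3.9%, and 0 to about 2.7 points of power are lost against a site-adjusted model.

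This rests on exact balance within site, on a site share that the documents do not give, and on site being absent from the undescribed part of the LMM. A reader might take the mismatch as a threat to validity. The documents do not support that: the LMM estimate is not biased, the false-positive rate is not inflated, and the requirement of 95 per arm is unaffected. It is a nearly free improvement, not a flaw that endangers the conclusion.

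**What to change.** Add the randomisation site as a fixed effect to the LMMs for the primary and secondary continuous outcomes, or state that it is already included. A fixed effect is preferable to a random one if sites are the three named organisations, because three levels are too few to estimate a variance well. Define site in the same sentence. The cost is 2 degrees of freedom for three organisations and more if sites are local services.

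Add site to the logistic GEE as well, and say that the odds ratio is then conditional on site, or report a standardised marginal effect from the adjusted model. Extending the term to the cost and effect regressions is optional: the health-economic paragraph already provides for regression adjustment, though only for baseline imbalance in costs and outcomes.

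Site must be known for every patient for the allocation to be carried out as described, so no new data are needed and nothing changes for patients or clinics. Fixing the term in advance also removes a later choice between adjusted and unadjusted results.

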### Concealment mechanism {16b}

The independent randomization bureau is the only staff with access to the randomization sequence, and they will keep this concealed from all others. Therefore, researchers and therapists cannot know beforehand to which group a new included participant will be allocated.

### Implementation {16c}

Trial assessors will enrol participants in the trial. Our independent randomization bureau will generate the allocation sequence and assign participants to the interventions. After randomization of a new participant, trial therapists receive an email from the randomization bureau with the allocated intervention. The therapists inform the participant about the allocation and start the therapy.

## Assignment of interventions: blinding

### Who will be blinded {17a}

The trial assessors will be blind to group allocation, but participants, peer counsellors, and therapists will not be.

### Procedure for unblinding if needed {17b}

In case of unblinding during an assessment by a participant, the assessment is stopped and finished by another trial assessor. The unblinded trial assessor will also not execute future assessments with the specific participant. The number of unblinding incidents will be registered.

## Data collection and management

### Plans for assessment and collection of outcomes {18a}

Assessments will be conducted by trained trial assessors to promote data quality. Table 1 presents an overview of the instruments used.

#### Demographic characteristics: to determine demographics at recruitment

These include age, gender, cultural identity, education, employment, living condition, relationship status, duration of being in mental healthcare and previous experience with CBT.

#### WEMWBS: to assess mental wellbeing

The Warwick-Edinburgh Mental Well-Being Scale (WEMWBS)^28^ is a 14-item self-report questionnaire covering both feeling and functioning aspects of mental wellbeing. The scale has been widely used for monitoring and investigating the determinants of mental wellbeing. The WEMWBS has excellent psychometric properties in terms of reliability and validity.

#### PSYRATS: to assess persecutory delusions

The Psychotic Symptom Rating Scales-Delusions Subscale (PSYRATS-DS)^42^ consists of six items which assess the following dimensions of delusions: frequency of preoccupation with delusions, duration of preoccupation with delusions, conviction, frequency of distress, intensity of distress and disruption to life caused by beliefs. Test–retest reliability has been found to be high [57]. Scores on the PSYRATS can be used to calculate factors relating to frequency and distress, which have a reported ICC of 0.93 and 0.87, respectively [58].

#### R-GPTS: to assess paranoid ideation

The Revised-Green et al., Paranoid Thoughts Scales (R-GPTS) is an 18-item self-report questionnaire that assesses ideas of persecution (10-item) and social reference (8-item) and was found to have excellent psychometric properties [59]. A hierarchical relationship between social reference and persecution was found.

#### Time-budget measure: to measure activity

The time budget measure is used to assess (social) activity. The measure is specifically designed for people experiencing psychosis [60].

#### CHOICE: to assess patient satisfaction

The CHoice of Outcome In Cbt for psychosEs (CHOICE) short form [61] is a 12-item self-report questionnaire examining satisfaction with therapy using patient definitions of recovery and therapy aims.

#### TIC-P and EQ-5D-5L: to assess resource use and quality-adjusted life years

Resource use will be measured with the Trimbos Institute and iMTA Cost Questionnaire for Psychiatry (TIC-P), short version. Using the TIC-P, we will measure healthcare usage, patients’ and their family’s out-of-pocket costs, and productivity losses owing to absenteeism and presenteeism. The EuroQol 5-dimension 5-level questionnaire (EQ-5D-5L) will be used to measure health-related quality of life (HRQoL). The EQ-5D-5L describes health states over five domains of mobility, self-care, usual activities, pain/discomfort, and anxiety/ depression. Dutch tariffs [62] will be applied to each of the health states to obtain utilities, in which 0 represents death and 1 full health. Next, utilities will be combined over time by calculating the area under the curve (or linear interpolation) to calculate quality-adjusted life years (QALYs).

#### TALE: to assess past-traumatic experiences at recruitment

The Trauma And Life Events checklist (TALE) is a 21-item checklist for traumatic experiences and shocking life events in people with psychotic disorders that was recently developed [63]. It covers all main categories of trauma (abuse and neglect) and bullying, stressful psychotic experiences, experiences of loss, and stressful experiences in contact with mental health or criminal justice services.

#### CRF-S: to assess the participant’s view of the therapist

The Counsellor Rating Form – Short (CRF-S) [55] is a 12-item self-report questionnaire that assesses the counsellor’s attractiveness, expertness and trustworthiness as perceived by the participant on a 7-point Likert scale ranging from 1 (‘not at all’) to 7 (‘very’). The CRF-S has been shown to be psychometrically robust.

#### WAI-SR: to assess therapeutic alliance

The Working Alliance Inventory – Short Form Revised [56] (WAI-SR) is a 12-item self-report questionnaire that assesses the strength of the therapeutic alliance on a 5-point Likert ranging from 1 (‘rarely or never’) to 5 (‘always’). The WAI-SR has been shown to have high construct validity, test–retest reliability, and internal consistency [56].

#### TSQ: to screen for PTSD diagnoses

The Trauma Screening Questionnaire (TSQ) is a 10-item self-report questionnaire that assesses post-traumatic stress symptoms [43]. The scale has five re-experiencing items and five arousal items. A score ≥ 6 on the TSQ is indicative of the probability of PTSD diagnosis in people with psychosis [44].

#### PCL-5: to assess the severity of PTSD symptoms

The PTSD Checklist for the DSM-5 (PCL-5) is a 20-item self-report questionnaire assessing PTSD symptoms. The questionnaire has been validated in many different types of samples [64]. The DSM-5 version was recently found to demonstrate strong validity and reliability [45]. PCL-5 item scores are summed to yield a continuous PTSD symptom severity score.

#### ISI: to assess insomnia

The Insomnia Severity Index (ISI) is a 7-item self-report questionnaire that assesses the severity of both night-time and daytime components of insomnia [46].

#### BCSS: to assess beliefs about self and other people

The Brief Core Schema Scales (BCSS) is a 24-item self-report questionnaire that assesses schemata concerning self and other people [47]. The questionnaire assesses four dimensions of self and other evaluation: negative-self, positive-self, negative-other, positive-other.

#### DWQ: to assess worry

The Dunn Worry Questionnaire (DWQ) is a 10-item questionnaire that assesses general problematic worry [48]. The scale has demonstrated excellent internal reliability, test–retest reliability, concurrent validity, and sensitivity to change.

#### VIS: to assess the impact of auditory verbal hallucinations

The Voice Impact Scale (VIS) is a 24-item self-report questionnaire that assesses the impact of voices. It contains three 8-item subscales: negative impact of voices, positive impact of voices, and living well with voices. The psychometric qualities of the VIS are good. A publication about the psychometrics is underway.

